#### Additional measures

*Demographics:* demographic variables, including age, sex, and level of education of both the caregiver and the care recipient, will be assessed during a demographical interview with the caregiver. Furthermore, information about the type, severity, and duration of dementia, caregiver hours of contact with the PwD, caregiver hours of caring for the PwD, and PwD hours spent in a dementia day care setting will be collected. The Clinical Dementia Rating scale (CDR) will be used to stage the severity of the dementia [35]. The CDR score is rated on a 5-point scale: 0 = ‘normal’; 0.5 = ‘very mild dementia’; 1 = ‘mild dementia’; 2 = ‘moderate dementia’; and 3 = ‘severe dementia’. The CDR has become widely accepted in the clinical setting as a reliable and valid global assessment measure of dementia [36].

*Neuropsychiatric symptoms in the PwD:* the Neuropsychiatric Inventory Questionnaire (NPI-Q), a brief form of the Neuropsychiatric Inventory (NPI), will be used to evaluate neuropsychiatric symptoms in the PwD and associated caregiver distress [37]. The NPI-Q evaluates twelve neuropsychiatric domains, including: delusions, hallucinations, agitation/aggression, dysphoria/depression, anxiety, euphoria, apathy, disinhibition, irritability, aberrant motor behavior, nighttime behavioral disturbances, and appetite and eating abnormalities. For each domain, the caregiver answers a screening question to indicate whether the symptom is present or not. If present, the severity is rated on a scale from 1 (mild) to 3 (severe). Total sum scores range from 0 to 36. Additionally, a caregiver distress score is rated for each domain on a 6-point scale, ranging from 0 (not emotionally stressful) to 5 (extremely stressful). The Dutch version of the NPI-Q has been investigated and appears to be a valid instrument [38].

*Quality of the relationship:* quality of the relationship will be assessed using four items of the University of Southern California Longitudinal Study of Three-Generation Families measures of positive affect [39]. The items represent: general closeness, communication, similarity of views on life, and degree of getting along with each other. Answer scales range from 1 (not at all) to 4 (very). Caregivers will answer these items in terms of the current situation and to what extent the relationship changed since illness onset (1 = much better, 5 = much worse). Summed scores will be used as an index of the change in relationship quality. A previous study found good internal reliability [40].

*Coping:* the 44-item Utrechtse Coping List (UCL) will be used to measure seven different coping strategies in the caregiver, including seeking distraction (eight items), expressing emotions (three items), seeking social support (six items), avoiding (eight items), fostering reassuring thoughts (five items), passive coping (seven items), and active coping (seven items). Items are rated on a 4-point scale, ranging from 1 (rarely or never use this strategy) to 4 (very often use this strategy). The reliability and validity has been found sufficient despite some inconsistencies in the literature [41].

*Personality:* the 12-item Neuroticism domain of the NEO Five-Factor Inventory (NEO-FFI) will be used to identify subjects who are susceptible to psychological distress. This domain measures six traits: anxiety, angry hostility, depression, self-consciousness, impulsiveness, and vulnerability. Item scores will be rated on a 5-point scale, ranging from 0 (strongly disagree) to 4 (strongly agree), and will be accumulated to generate a total sum score (range 0–48). The reliability and internal consistency of the Dutch version of the NEO-FFI is good [42].

#### Outcome measures in the process evaluation

As part of the process evaluation, sampling quality and intervention quality will be evaluated to determine the internal and external validity of the intervention program and to reveal facilitators and barriers for the intervention.

*Sampling quality*: will be evaluated by describing (1) the recruitment and randomization procedure; (2) the informed consent and allocation procedure; and (3) barriers and facilitators to the recruitment of caregivers. Reach will be established by the proportion of caregivers participating and the number of institutions involved in the intervention.

*Intervention quality:* will be evaluated by determining (1) the relevance of the intervention; (2) the feasibility of the intervention; and (3) the extent to which the intervention was performed according to protocol.

Required data will be collected from the research database, and during the sessions with the coach and the post-intervention assessment. Objective measures of compliance with respect to the ESM procedure (number of completed beeps) and the intervention (number of drop-outs) will be examined. Technical problems with the PsyMate will be logged. Subjective experiences with respect to the intervention (i.e. clearness, relevance, usability, impact on daily functioning, satisfaction with procedure and time burden, suggestions for improvement, and recommendations to other caregivers) will be assessed by means of a quantitative questionnaire and a qualitative interview with the caregiver during the third feedback session. In addition, subjective experiences with the PsyMate and ESM procedure (e.g. difficulties operating the device, clearness items, readability of the items on the screen, interference with daily activities, and reasons for missed beeps) will be examined.

Performance of the intervention according to protocol will be evaluated with a structured registration form, which includes protocol deviations and duration of each face-to-face session during the intervention period.

#### Economic evaluation

The economic evaluation will involve a cost-effectiveness analysis (CEA) and includes the assessment of costs as well as outcomes of the intervention.

*Resource use and costs:* the Resource Utilization in Dementia – shortened version (RUD-lite) will be used to map the utilization of resources for both the PwD and the caregiver [43]. The RUD-lite assesses both formal and informal resource use, making it possible to calculate costs from a societal point of view. Costs will be calculated by multiplying the quantity of resource use by the cost price per resource unit and will include the period from the baseline assessment until the last follow-up assessment (6 months). All relevant costs will be determined according to the Dutch guidelines for cost calculations in health care [44].

*Intervention costs:* intervention costs will include the amount of time spent on briefing the caregivers regarding the PsyMate and ESM procedure, the feedback sessions with the coach, administration (e.g. writing short feedback reports), telephone contact, the training session for the coach on how to provide the feedback, and costs of required materials (e.g. PsyMate). The coach will register the duration of the feedback sessions, administration, and telephone contact with the caregiver on a structured registration form. Incremental cost effectiveness ratios (ICER) will be calculated by dividing the difference in total costs between the treatment arms by the difference in average effect size.

*Quality of life:* caregivers’ health related quality of life will be measured with the EuroQol-5D (EQ-5D) and consists of five items representing the following dimensions mobility, self-care, usual activities, pain/discomfort, and anxiety/depression [45]. Respondents indicate their health state by rating each dimension on a 3-level scale, including 1 ‘no problems’, 2 ‘moderate problems’, or 3 ‘severe problems’. In addition, the EQ-VAS will be used to record caregivers’ self-rated health status on a Visual Analogue Scale, anchored at ‘the best health you can imagine’ (100) and ‘the worst health you can imagine’ (0). The EuroQol demonstrates a good test-retest reliability [46]. For the cost-effectiveness analysis, quality-adjusted life-years (QALYs) will be calculated according to the Dutch EuroQol tariff [47].

### Sample size

The calculation of the sample size will be based on previous studies using the Sense of Competence Questionnaire (SCQ) as outcome measure in intervention studies for caregivers of PwD, the use of repeated measures, within-between interaction with a mean effect size of 0.8 [48], and the following assumptions: alpha 0.05, 80 % power and 25 % loss to follow up. Accordingly, we aim to enrol 90 participants in the study (30 participants per group).

### Statistical analyses

#### Primary and secondary outcome measures

Data will be entered twice to guarantee data integrity. Before the analyses, data will be checked for missing values and handled according to their distribution (missing completely at random, missing at random, or not missing at random), and the ‘intention-to-treat’ principle. Additionally, data will be checked for outliers, and normality. Non-parametric tests will be used in case of non-normality after data transformation. Possible baseline differences in group characteristics will be tested with t-tests for continuous and *χ*^2^-tests for categorical variables.

To investigate changes in the primary and secondary outcomes for each group during the intervention period, an analysis of covariance (ANCOVA) will be performed with outcome at post-intervention as the dependent variable, group (experimental, pseudo-experimental, control) as the between-subject factor, and outcome at baseline and potential confounders (e.g. demographic variables, coping, personality, and quality of the relationship) as covariates. Separate analyses will be conducted for each outcome variable. Group differences in the post-intervention outcome, adjusted for the baseline value, will be examined to test the effectiveness of the intervention. In case group differences are present, the inter-group effect size will be calculated using Cohen’s *d*.

To examine changes in the primary and secondary outcomes for each group during the total study period, a linear mixed model (LMM) for repeated measures will be conducted. Analyses will be performed with group as a fixed between-subject factor (3 levels: experimental, pseudo-experimental, and control group) and time as fixed within-subject variable (4 levels: baseline, post-intervention, two-month follow-up, and six-month follow-up) and first-order interactions as additional fixed factors. The LMM will estimate fixed effects (regression slopes) for change in the intervals during (T0-T1) and after (T1-T2, T2-T3) the intervention period. The intervals will be entered as a categorical dummy variable (3 levels). Potential confounders will be added to the model as covariates. Additionally, coach will be added as a random factor to estimate the variability ascribed to the coach.

All data will be analysed using STATA 12.1 [49]. Tests of significance will report mean change and will be two tailed with *α* set at 0.05.

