### Study procedure

#### Baseline assessment (T0)

After the randomization procedure, a baseline assessment (T0) will take place in the caregiver’s home or at the MUMC+ according to their preference. Participants will be asked by the research assistant to sign the informed consent before continuation of the study procedure. Next, a demographical interview will be conducted to assess caregiver and care recipient characteristics. Additionally, caregivers will be asked to participate in a 3-day ESM baseline measurement, starting the day after the baseline assessment. A 30-min briefing will be provided during the baseline assessment to ensure that they fully understand the procedure and how to operate the PsyMate. A demo questionnaire will be presented to familiarize caregivers with the device and a leaflet containing all relevant information regarding the use of the device will be handed out. Finally, the caregivers will be asked to complete a number of retrospective questionnaires at their own convenience as part of the effect evaluation.

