### Instruments

For an overview of the instruments used during the baseline, post-intervention and follow-up assessments see Table 2.

**Table 2 Tab2:** Flowchart of measures used during the assessments

	Pre-test	Intervention period			Post-tests		
	T = 0	FB1	FB2	FB3	T = 1	T = 2	T = 3
Primary outcome measures RCT							
- Sense of competence: SSCQ	X				X	X	X
- Perceived control: PMS	X				X	X	X
Secondary outcome measures RCT							
- Depressive symptoms: CES-D	X				X	X	X
- Perceived stress: PSS	X				X	X	X
- Anxiety symptoms: HADS-A	X				X	X	X
ESM outcome measures RCT							
- Momentary positive affect	X				X		
- Momentary negative affect	X				X		
Additional measures RCT							
- Demographic variables	X						
- Neuropsychiatric symptoms in PwD: NPI-Q	X				X	X	X
- Quality of the relationship: 4 items of the University of Southern California Longitudinal Study of Three-Generation Families measures of positive affect	X				X	X	X
- Coping: UCL	X				X	X	X
- Personality: subscale neuroticism of NEO-FFI	X				X	X	X
Outcome measures process evaluation							
- Subjective experiences with intervention: quantitative questionnaire & qualitative semi-structured interview				X			
- Subjective experiences with the use of the ESM device: quantitative questionnaire					X		
- Subjective experiences with ESM procedure: quantitative questionnaire		X	X	X	X		
Outcome measures economic evaluation							
- Resource use: RUD-lite	X				X	X	X
- Quality of life: EQ-5D	X				X	X	X

*RCT* randomized controlled trial, *SSCQ* Short Sense of Competence Questionnaire, *PMS* Pearlin Mastery Scale, *CES-D* Center for Epidemiological Studies Depression Scale, *PSS* Perceived Stress Scale, *HADS-A* Hospital Anxiety and Depression Scale, Anxiety subscale, *PwD* person with dementia, *NPI-Q* Neuropsychiatric Inventory Questionnaire, *UCL* Utrechtse Coping List, *NEO-FFI* NEO Five-Factor Inventory, *ESM* Experience Sampling Methodology, *RUD-lite* Resource Utilization in Dementia – shortened version, *EQ-5D* EuroQoL-5D

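### A normality check decides whether the primary outcomes keep the baseline-adjusted analysis or pass to an unnamed non-parametric test that need not answer the same question

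*Protocol article*

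**What the plan says.** All of this stands in the protocol article under Statistical analyses, Primary and secondary outcome measures, unless noted.

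- **Switching rule.** Before the analyses, data are checked for outliers and normality, and then: "Non-parametric tests will be used in case of non-normality after data transformation". No test, no criterion and no replacement model is named.
- **Test of effectiveness.** An ANCOVA of the post-intervention outcome on group and baseline value. "Group differences in the post-intervention outcome, adjusted for the baseline value, will be examined to test the effectiveness of the intervention". Where groups differ, Cohen's d follows, and the section ends by saying that significance tests report mean change.
- **Whole study period.** A linear mixed model with three groups, four time points and their interaction.
- **Covariates.** The ANCOVA takes "outcome at baseline and potential confounders (e.g. demographic variables, coping, personality, and quality of the relationship) as covariates". The mixed model says only: "Potential confounders will be added to the model as covariates". A time point is attached to the outcome but not to the other covariates.
- **Repeat measurement.** Table 2 under Instruments schedules coping, relationship quality and "Personality: subscale neuroticism of NEO-FFI" at T0, T1, T2 and T3.

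**The concern.** The plan fixes one target, a baseline-adjusted mean difference, and then lets a look at the data replace the method that estimates it. A Mann-Whitney or Kruskal-Wallis test on post scores ignores the baseline value and yields no mean change. No standard rank test replaces the group-by-time mixed model either. Two outcomes of the same trial could thus be tested for different quantities, depending on how each distribution happened to look. The normality assumption of ANCOVA and of the mixed model concerns residuals, while the text speaks only of checking data.

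At stake are the estimand and power in a small trial. A lesser matter is that covariates without a time point could be entered as repeated values, and some of these lie downstream of the intervention.

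**Working it through.** **1. The plan's own figure.** The Sample size section gives effect size 0.8, alpha 0.05, 80% power, 25% loss and 90 participants. Reading 0.8 as Cohen's d, so f = 0.8/2 = 0.4, with 3 groups and 2 time points, the within-between interaction F test with noncentrality f²(N − 3)(2 − 1) needs N = 67: 0.16 × 64 = 10.24. Then 67/0.75 = 89.3, rounded up to 90. The figure is reproducible, although f and the number of time points are assumptions. The sample size is not in dispute. Completers per arm are 30 × 0.75 = 22.5, so 22 are used below.

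**2. What baseline adjustment is worth.** ANCOVA multiplies the error variance by (1 − r²), where r is the baseline-outcome correlation. Dropping the adjustment multiplies the variance by 1/(1 − r²): 1/0.91 = 1.10 at r = 0.3, 1/0.75 = 1.33 at r = 0.5, 1/0.51 = 1.96 at r = 0.7. The documents give no r; this range is assumed.

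**3. Simulated power**, two-arm contrast, 22 per arm, d = 0.8, two-sided 5%:

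| Data | Method | r = 0.3 | r = 0.5 | r = 0.7 |
|---|---|---|---|---|
| Bounded 7–35 sum score with ceiling, normality check triggered | ANCOVA | 73% | 80% | 92% |
| | Mann-Whitney, post score | 69% | 70% | 70% |
| Normal | ANCOVA | 75% | 84% | 95% |
| | Mann-Whitney, post score | 70% | 72% | 71% |
| Lognormal, not transformed | ANCOVA | 78% | 84% | 93% |
| | Mann-Whitney, post score | 90% | 91% | 92% |
| | Rank ANCOVA | 92% | 96% | 99% |

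The bounded score is the closest match to the SSCQ, whose range is 7–35. There the loss is 73 − 69 = 4, 80 − 70 = 10 and 92 − 70 = 22 points from the rounded figures (roughly 4, 11 and 22). The lognormal rows show the opposite for ANCOVA against the unadjusted rank test at r = 0.3 and 0.5, near equality at r = 0.7, and rank ANCOVA ahead of both throughout.

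**4. Type I error.** With no true effect, choosing between ANCOVA and Mann-Whitney by a Shapiro-Wilk test rejected in 4.7% to 5.9% of runs. The switch does not inflate alpha in any material way.

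**5. Secondary point: covariate timing.** If treatment shifts a covariate by a SD and the outcome depends on that covariate with slope b, adjusting for its T1 value removes a × b of the effect, a share of ab/0.8. For a = 0.2, b = 0.3 this is 0.06/0.8 = 7.5%. For a = 0.4, b = 0.5 it is 0.20/0.8 = 25%. For a = 0.8, b = 0.5 it is 0.40/0.8 = 50%. The simulated estimates were 0.74, 0.61 and 0.40, against about 0.80 with the T0 value; in the last case power fell from about 88% to 39%. The values of a and b are assumptions. The Background and the Discussion both describe positive emotions as helping caregivers to cope, so the article itself places coping on the intervention's pathway.

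**The case against.** The strongest defence is that the plan names no rank test. Rank ANCOVA would keep the baseline value, and the sentence on effectiveness could be read as requiring that. Transformation also comes first, so the fallback is meant for data that remain awkward, and the lognormal rows show that even an unadjusted rank test can then do better than ANCOVA. With normal data the check fails in only about 5% of runs, so the two-step rule as a whole cost at most about one power point there (94.5% to 93.6% at r = 0.7).

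Much of this stands. The power loss is conditional on the switch being made and on an unadjusted test being chosen. It does not answer the main point: a plan that defines its effect as an adjusted mean difference should not leave open a route to a test that estimates something else. The lognormal case is also the one that a log transformation would largely remove, and rank ANCOVA is better than the unadjusted test even there.

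Three stronger readings are tempting and are not supported:

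- **That the baseline tests steer the model.** The article says "Possible baseline differences in group characteristics will be tested with t-tests for continuous and" chi-square tests for categorical variables, and stops. No sentence lets the results select covariates, and the confounders are named by content. Chance differences at baseline therefore have no stated consequence for the analysis.
- **That post-intervention covariates will be used.** The text is silent on timing. A baseline reading is natural, since demographics, the first example, are collected only at T0.
- **That the dividing line is randomisation.** "After the randomization procedure, a baseline assessment (T0) will take place", so T0 values are themselves measured after randomisation. The line that matters is the start of the intervention.

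**Conclusion.** The concern holds in limited form. The switching rule conflicts with the plan's own definition of effectiveness and its stated reporting of mean change, and it has no workable counterpart for the mixed model. Its cost, if an unadjusted rank test is used on bounded scores, is roughly 4, 11 and 22 power points at r = 0.3, 0.5 and 0.7. This rests on d = 0.8, about 22 completers per arm, the assumed correlations and the assumed score distribution. It is not a general law: under strong skew left after transformation the unadjusted rank test can gain power over ANCOVA. Type I error is not at issue, and nor is the sample size. The missing time point for covariates is a secondary wording matter; the 7.5% to 50% attenuation shows what a T1 value could do, not what the plan says will be done.

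**What to change.** - State that the baseline-adjusted ANCOVA (T0 to T1) and the mixed model (all time points) are the analyses of the primary and secondary outcomes whatever the normality check shows, and delete the switch to non-parametric tests.
- Judge assumptions on model residuals, and use robust or bootstrap standard errors where these look poor.
- Name a baseline-adjusted rank ANCOVA as a sensitivity analysis.
- State that coping, neuroticism and relationship quality enter any model only as T0, pre-intervention values.

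The change is to wording only: no extra data, visits or participants. The price is some loss of power in the main analysis if residuals are strongly skewed (78% against 92% for rank ANCOVA in the lognormal case at r = 0.3), which the rank ANCOVA sensitivity analysis would bring to light.

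### Cohen's d from the post-intervention ANCOVA is calculated only when a group difference is found, which inflates the reported d for small true effects and leaves null contrasts without one

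*Protocol article*

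**What the plan says.** In the protocol article, under Statistical analyses (Primary and secondary outcome measures), each outcome is analysed by ANCOVA. The post-intervention score is the dependent variable, the three-level group is the factor, and the baseline value and potential confounders are covariates. The purpose is stated as: "Group differences in the post-intervention outcome, adjusted for the baseline value, will be examined to test the effectiveness of the intervention". The next sentence is: "In case group differences are present, the inter-group effect size will be calculated", with Cohen's d as the measure. The article does not define when a difference counts as present, nor whether the overall three-group test or a pairwise comparison decides it. The significance level in the same section is 0.05.

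Two other statements there carry no such condition: "Tests of significance will report mean change and will be two tailed", and "The LMM will estimate fixed effects (regression slopes) for change in the intervals" during and after the intervention.

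The Sample size section fixes the scale: "we aim to enrol 90 participants in the study (30 participants per group"), with "25 % loss to follow up" and a planning effect size of 0.8 whose type is not named.

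**The concern.** This is a positive instruction, not a gap that an analysis plan would fill: the only standardised effect size named for these outcomes depends on the test result. When an estimate is kept only if it is significant, its expected value exceeds the truth, and the excess grows as power falls.

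Three features of this trial make that relevant. The Background says that earlier caregiver interventions had small effects, which is where the selection bias is largest. The pseudo-experimental arm exists to show whether feedback adds anything to self-monitoring, and the article itself suggests that self-monitoring alone may help; that contrast could well be small and so lose its d. The trial also takes its own sample size from a published effect size, and later trials may use its d in the same way.

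At stake is how readers and meta-analysts judge the size of the effect. The hypothesis tests are not at stake.

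**Working it through.** **Inputs from the article.** 30 per arm; 25 % loss, so 30 × 0.75 = 22.5, taken as 22; two-sided alpha 0.05; planning effect 0.8. Loss by the post-intervention visit may be less than 25 %, so 22 and 30 per arm bracket the case.

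**Assumed, because the article does not give them.** True d of 0.3, 0.5 or 0.8; correlation r of the outcome with baseline from 0 to 0.7; pseudo-experimental mean equal to control or midway between control and experimental.

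**The plan's own figure.** The effect-size type and the repeated-measures correlation are not stated, so the named calculation cannot be repeated. An overall three-group F test with f = 0.8/2 = 0.4 needs 22 per arm; 22/0.75 = 29.3, rounded up to 30, and 3 × 30 = 90, which matches. The point made here does not depend on how 90 was reached.

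**Step 1: smallest pairwise d that is significant.** d_min = t(0.975, 2n − 2) × √(2/n) × √(1 − r²).
- n = 22, r = 0: 2.018 × 0.3015 = 0.61. With r = 0.5: 0.608 × 0.866 = 0.53.
- n = 30, r = 0: 2.002 × 0.2582 = 0.52. With r = 0.5: 0.517 × 0.866 = 0.45.

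If the pairwise test is the gate, an observed d below these values is not reported.

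**Step 2: how often a d is reported.** With the pairwise gate and r = 0, a true d of 0.3 is significant in 16 % of trials at 22 per arm and 21 % at 30. A true d of 0.8 is significant in 74 % and 86 %.

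**Step 3: mean reported d divided by true d.** Three-arm ANCOVA was simulated for the experimental versus control contrast, with the adjusted difference divided by the pooled within-group SD (60,000 trials per setting). Each cell gives the range over 22 to 30 per arm, r from 0 to 0.7, and both placements of the pseudo-experimental arm.

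| True d | Pairwise gate | Overall F gate | Both required |
|---|---|---|---|
| 0.3 | 1.65–2.54 | 1.53–2.44 | 1.74–2.79 |
| 0.5 | 1.16–1.65 | 1.12–1.71 | 1.19–1.79 |
| 0.8 | 1.01–1.19 | 1.01–1.24 | 1.02–1.25 |

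With the outcome SD taken as known instead of estimated, the pairwise column becomes 1.63–2.44, 1.15–1.60 and 1.01–1.16. Rounded, the ranges are about 1.6 to 2.8 at 0.3, 1.15 to 1.8 at 0.5 and 1.0 to 1.25 at 0.8. One corner falls slightly below them: overall F gate, 30 per arm, r = 0.7, pseudo-experimental equal to control, with 1.53 at 0.3 and 1.12 at 0.5.

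**Step 4: without the gate.** In the same simulations the mean d over all trials was 0.30 to 0.31 for a true 0.3. The condition therefore causes the inflation, apart from the usual small-sample excess of 1 to 2 %.

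**The case against.** The strongest reply is that the rule reaches only one statistic. Mean change and the mixed-model fixed effects are reported whatever the result, and the mixed models cover every primary and secondary outcome. A reader might infer that every reported effect size is selected, or that a null contrast is left with no estimate at all. The article supports neither. Only the standardised d from the post-intervention ANCOVA is conditional, and d could be recovered if group means and SDs are published. Silence on confidence intervals is no fault in a condensed article. This part of the reply stands and sets the scope of the point.

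Second, the gate is undefined. If it is the overall three-group test, passing it releases all three pairwise d values, small ones included. In simulations at 22 per arm with r = 0.6, about 35 to 48 % of the released values lay below 0.48, roughly the pairwise threshold there. So it cannot be said that every reported d was selected for being large. That also stands, but the overall F column in the table shows the average still inflated.

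Third, a reader might take a two-fold overstatement as the general size. It fits only a true d near 0.3, and at the effect the trial was planned for the bias is modest.

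What the reply does not remove is the rule itself. The ungated estimates are unstandardised, and the outcome scales have different ranges (7–35, 0–28, 0–60), so they do not do the job of d across outcomes.

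**Conclusion.** The point holds as a reporting defect of limited scope. Calculating Cohen's d only after a positive ANCOVA result biases the reported d upward whichever test is the gate. The bias is material if true effects are small to moderate and slight at the planned 0.8. Contrasts that do not pass get no standardised effect size; under an overall gate that means all three contrasts for that outcome.

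The multipliers rest on reading presence as significance at 0.05, on 22 to 30 completers per arm, and on assumed true effects and baseline correlations that the article does not supply. The direction of the bias does not depend on those values. Type I error, power, sample size and the test of effectiveness are unchanged.

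**What to change.** Replace the conditional sentence with: *The baseline-adjusted mean difference and Cohen's d, each with a 95 % CI, will be reported for all three pairwise group contrasts and for every primary and secondary outcome, regardless of statistical significance.*

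State in the same place which SD standardises d, so that values are comparable across outcomes. The cost is one or two sentences and a few more table cells. It needs no extra data and no change to sample size or alpha, and it removes the selection described above.

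### The whole-study mixed model takes baseline as an outcome level, so the two- and six-month persistence question gets no baseline-adjusted estimate and contrasts with T0 lose some precision

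*Protocol article*

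**What the plan says.** The section on primary and secondary outcome measures under Statistical analyses (protocol article) plans two models for each questionnaire outcome.

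- **ANCOVA at T1.** The covariates are "outcome at baseline and potential confounders (e.g. demographic variables, coping, personality, and quality of the relationship) as covariates". Its role is stated: "Group differences in the post-intervention outcome, adjusted for the baseline value, will be examined to test the effectiveness of the intervention".
- **Mixed model over all four assessments.** It has "group as a fixed between-subject factor (3 levels: experimental, pseudo-experimental, and control group"), "time as fixed within-subject variable (4 levels: baseline, post-intervention, two-month follow-up, and six-month follow-up"), and "first-order interactions as additional fixed factors". It is to estimate "change in the intervals during (T0-T1) and after (T1-T2, T2-T3) the intervention period". On covariates it says only: "Potential confounders will be added to the model as covariates".

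The ANCOVA sentence lists the baseline outcome separately from the potential confounders, so the confounders added to the mixed model do not include it. No common-baseline constraint is stated.

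Study aims makes it an objective to see whether effects persist two and six months after the intervention. Table 2 schedules both primary outcomes at T0 and at all three later assessments. The mixed model is the only analysis described for T2 and T3.

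**The concern.** With a free group effect at T0, a group x time term that contrasts a later visit with T0 compares mean changes between arms. It does not compare later values adjusted for where each caregiver started. A covariate that is constant over time does not alter this.

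Two things follow. The T0-T1 effect gets a second estimate that differs from the ANCOVA. More importantly, any statement about benefit at two or six months relative to the start rests on the less precise contrast, and the plan offers no adjusted group difference at those visits. In a three-arm trial of 90 caregivers that expects 25% loss, precision at follow-up matters.

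**Working it through.** **Inputs.** From Sample size: 30 per arm, 25% loss, effect size 0.8, alpha 0.05. Tests are two-sided (Statistical analyses). After loss, n = 30 x 0.75 = 22.5 per arm. The correlation r between T0 and a later score is not given, so it is varied. The SD is taken as equal over time and set to 1.

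**The plan's own figure.** The article states no precision for either model. Its total of 90 is matched by a one-way three-group ANOVA with f = 0.4: 66 in total, 22 per arm, and 22/0.75 = 29.3, rounded up to 30. That total does not bear on this point.

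**Formulas, complete data.** Variance of the difference between two arms:
- change score: (2/n) x 2(1-r)
- adjusted for T0: (2/n) x (1-r²)
- ratio, adjusted to change: (1-r²) / [2(1-r)] = (1+r)/2
- power ≈ Φ(d/SE - 1.96)

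Example, r = 0.5, d = 0.8. Adjusted SE = √(2/22.5 x 0.75) = 0.258, and 0.8/0.258 - 1.96 = 1.14, so power is 0.87. Change-score SE = √(2/22.5 x 1) = 0.298, and 0.8/0.298 - 1.96 = 0.72, so power is 0.77.

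| r (assumed) | Variance ratio | SE of change score larger by | Power at d = 0.8, adjusted v change | Power at d = 0.5, adjusted v change |
|---|---|---|---|---|
| 0.3 | 0.65 | 24% | 0.80 v 0.62 | 0.42 v 0.29 |
| 0.5 | 0.75 | 15% | 0.87 v 0.77 | 0.49 v 0.39 |
| 0.7 | 0.85 | 8% | 0.96 v 0.93 | 0.65 v 0.58 |
| 0.8 | 0.90 | 5% | 0.99 v 0.99 | 0.80 v 0.76 |

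**With missing follow-up.** The mixed model also uses the T0 scores of those who drop out, so it does somewhat better than a pure change score. With all T0 scores present and 25% of T1 missing at random, its variance relative to the ANCOVA is 1 + 0.75(1-r)/(1+r): 1.25 at r = 0.5, 1.13 at 0.7 and 1.08 at 0.8. In the example its SE is 0.258 x √1.25 = 0.289, and 0.8/0.289 - 1.96 = 0.81, so power is 0.79 rather than 0.77.

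**Check on the model as written.** In one simulated complete data set (30 per arm, r = 0.5), the group x T1 coefficient was 0.549, identical to the raw difference in mean change, and adding a time-constant covariate left it there. The ANCOVA on the same data gave 0.595, with SE 0.191 against 0.232. Over 6,000 simulated trials per scenario both estimators were unbiased. The change-to-adjusted variance ratio was 1.28 to 1.35 at r = 0.5 (formula 1.33) and 1.14 to 1.17 at r = 0.7 (formula 1.18). With 22 per arm, the two T1 tests disagreed on significance in 19% of trials (r = 0.5, d = 0.5), 15% (0.7, 0.5), 14% (0.5, 0.8) and 5% (0.7, 0.8).

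**Intervals after T1.** T1-T2 and T2-T3 do not contain T0. With equal correlations between visits, adjusting for T0 leaves their variance unchanged (ratio 1.00). With first-order autoregressive correlation and r = 0.7:
- T1-T2: 1 - (0.49-0.70)²/0.6 = 0.93
- T2-T3: 1 - (0.343-0.49)²/0.6 = 0.96

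**The case against.** The strongest reply is that the plan is coherent as it stands. It gives the two models different roles, with effectiveness at T1 resting on the ANCOVA and the mixed model describing change over the whole study. The named post-intervention intervals suit a question about whether effects last, and they involve no baseline. The sample size is itself framed as a within-between interaction. If r is 0.7 or more, the loss at the design effect is small.

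Most of this stands, and it rules out three stronger readings that a reader might infer:

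- *That the two T1 analyses compete on equal terms for the primary conclusion.* The article ties the effectiveness test to the ANCOVA. What is missing is only a sentence saying that it prevails if the mixed model differs.
- *That every effect from the mixed model is inefficient.* The factor (1+r)/2 applies only to contrasts with T0.
- *That the mixed model is biased or inflates type I error.* Under randomisation both estimators are unbiased, and each test held its level in the simulations.

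The reply does not remove the gap at T2 and T3. Stability from T1 to T3 does not by itself show a benefit relative to the other arms. That needs a group difference at T2 and T3, and the plan provides one only through unadjusted change from T0.

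**Conclusion.** The point holds in limited form. The mixed model's contrasts with T0 are essentially raw change scores: exactly so with complete data, approximately so with missing data. With complete data, adjustment would cut their variance by 25% at r = 0.5, 15% at r = 0.7 and 10% at r = 0.8. With 25% of T1 missing, the cuts are 20% (1 - 1/1.25), 12% (1 - 1/1.13) and 7% (1 - 1/1.08). These figures rest on an assumed r and equal variances over time. The second T1 estimate is a minor matter because the ANCOVA has the named role. The main weakness is that persistence at two and six months has no baseline-adjusted estimate, although T0 is scheduled and the plan already adjusts for it at T1. The article fixes the factor levels and intervals itself, so this is a stated choice and not a detail left to a later document.

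**What to change.** Fit the mixed model to T1, T2 and T3 as outcomes, with T0 and T0 x time as covariates and group, time and group x time as fixed effects. Report the adjusted group difference at each of the three visits. Obtain the T1-T2 and T2-T3 changes as contrasts from the same model, so the intervals now named are kept. State that the ANCOVA result prevails at T1.

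This needs no new data, only a rewording of one model, but it has costs:

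- Participants without a T0 score drop out unless T0 is imputed, whereas the model as written keeps them. Such gaps are possible, because caregivers complete the T0 questionnaires in their own time (Baseline assessment). Those with only a T0 score also leave the model, but they carry no information on the adjusted effect.
- The T1 estimate equals the ANCOVA only with complete data and the same covariates and random terms. The planned mixed model has a random coach term that the ANCOVA lacks.
- T0 is measured after randomisation, and the blinding described is of the assessor. Like the planned ANCOVA, the revised model needs T0 answers to be unaffected by knowledge of allocation. Conditioning on T0 does not remove that requirement.
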